**Laboratory analyses**

Blood samples, slides and filter papers will be delivered to KEMRI/CDC laboratories in Kisumu. Here they will be processed to separate plasma and extract parasite DNA. Serological markers of malaria exposure will be determined in the microtainer-derived plasma samples, including IgG antibodies to malaria antigens [27]. We will also assay for antibodies to the circumsporozoite malaria antigen and to proteins and peptides which are components of mosquito saliva [28]. This will allow an assessment of recent exposure to both vectors and parasites. Microtainer-derived parasite DNA samples will be assayed using PCR to identify low-density parasite infections [29]. Filter paper blood samples will be taken as stable back-up sample for serum elution [16] and DNA extraction [29]. We will also use molecular techniques to look for markers that may be associated with treatment failures or contraindications for example *pfcrt, pfmdr,* or G6PD and markers associated with increased risk for contracting e.g. Duffy and transmitting malaria. A subsample (10%) of dried blood samples will be assayed for serology and related parasite PCR at LSHTM, UK and RUNMC, The Netherlands to ensure assay quality and quality assurance but the majority of laboratory analyses will be carried out at KEMRI/CDC Kisumu.

All questionnaires on the PDA will have the participant name, person ID, and barcode number. RDTs, slides, filter papers and blood samples will be labelled using the person ID and barcode number. No names will appear any of these samples. After the questionnaires are completed, the PDAs will be returned daily to the data management staff in the field for downloading and back up while the RDTs.

**10. DATA MANAGEMENT:**

a. Data storage

All data from the questionnaires during cross-sectional surveys will be collected on PDAs and downloaded each evening into Microsoft Access. Paper records will be used as a back-up to the PDAs for recording visited households and RDT and anaemia results. All consents, assents, PDAs and computers to which data are downloaded will be locked so that only the principal investigators and data management staff will have access to the data. Data will be cleaned on an on-going basis.

b. Data analysis

To assess the impact of the intervention, methods appropriate for cluster-randomized trials will be used [30]. The primary outcome will be PCR-confirmed parasitaemia. The prevalence by PCR in each cluster will be calculated and the unadjusted risk ratio (RR), or mean difference between clusters will be calculated. An overall estimate of programme impact will be obtained, and 95% confidence intervals will be adjusted for observed between-cluster variance. Formal hypothesis testing will be undertaken using stratified unpaired t-tests. Adjustment for covariates will be undertaken replacing the cluster means and proportions with covariate-adjusted residuals from regression analysis of individual-level data.

One of the key outcomes of the study is the community-wide effect of hotspot targeted interventions. To address the question of the distance over which this community-wide effect exists, we will relate parasite prevalence and antibody prevalence to the distance from the centre of the hotspot in intervention and control clusters.

Additionally, the analysis adjusts for baseline characteristics on malaria infection, haemoglobin concentration and socio-economic status. Statistical analysis will be carried out using STATA^®^ software, version 10.0. (Stata Corporation, Texas, USA).

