## c. Definition of clusters for interventions

## The data collected during the intensive cross-sectional surveys (SSC 1802) will be used to detect hotspots of malaria transmission in the study area based on malaria parasite prevalence and antibody responses. Hotspots will be defined as areas that are smaller than 1km^2^ with a level of transmission intensity that exceeds that in the surrounding area (in all directions). This will be indicated by a statistically significant higher parasite prevalence in combination with a statistically significant higher SCR and/or age-adjusted density of antibodies malaria antigens.

Malaria parasite prevalence will be determined by PCR-based detection of parasites based on the *P. falciparum* mitochondrial cytochrome b gene [15].

Malaria specific antibody responses will be quantified as the age-dependent seroconversion rate (SCR) for antibodies against malaria: antigens apical membrane antigen-1 (AMA-1), merozoite surface protein-1 (MSP-1_19_) and glutamate-rich protein (GLURP) [[12](#_ENREF_12)]. Antibody responses will be measured by standard ELISA methodology [12, 16] and the SCR will be determined by fitting a simple model to the age-dependent prevalence of antibody responses, as described in detail in publicly available protocols [16]. In addition, age-adjusted antibody densities will be calculated [17]. The SCR will be estimated for geographical subsets of 50 observations.

Hotspots will be of variable size and no quantitative estimate of the elevated transmission intensity inside hotspots can be given a-priori since this depends on the transmission intensity of the surrounding area [2-3,16]. Clusters will include hotspots and a surrounding ‘evaluation zone’ of 500m from the edge of the hotspot (see figure 2); this forms the unit of randomization. The grid structure that divided the study area into 250x250m cells, created as part of the baseline cross-sectional study will be used as easy references for the areas defined as hotspots. The size of a hotspot or intervention area will not be defined by the maximum mosquito dispersal range. We are not aiming to identify independent niches of malaria transmission. Minimum distance between hotspots will be 1km. Mosquito dispersal outside hotspots of malaria transmission is essential for the community effect and forms the cornerstone of our evaluation.

[figure not shown]

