## *Figure 2. Example of possible layout of hotspots (black blocks) and the surrounding areas (grey blocks) where hotspot targeted interventions will be evaluated). The depicted grid cells are 250x250m.*

## d. Intervention

Up to sixteen clusters will be defined as in the example shown in figure 2. Each cluster consists of a hotspot of malaria transmission and the area surrounding the hotspot 500m in each direction. In the entire study area current malaria control interventions will continue without interruption. In the intervention clusters (i.e. half of the identified hotspots), interventions will be superimposed on ongoing control measures: these intervention hotspots will be targeted with IRS, LLINs, larviciding and FSAT. All the intervention measures will be discussed in more detail in section f. ‘Procedures- Intervention Phase’ however, a brief overview is provided below.

*Indoor Residual Spraying (IRS)*

IRS will be carried out twice per year in all households in the intervention hotspots in the period preceding the long rainy season (March 2012) and six months later (September 2012). Meetings will be held with DOMC to discuss the optimal insecticide for use in the context of ongoing IRS activities in the district.

*Long Lasting Insecticide Treated Bednets (LLIN)*

All compounds in intervention hotspots will be visited in March 2012 and each house will receive a Long Lasting Insecticide Treated Nets for each sleeping space. The DOMC will be consulted about which type of LLINs should be distributed and how best to approach this, but activities will be undertaken by study personnel A follow-up visit is planned one month and 6 months after LLIN distribution to provide additional nets where needed and to monitor accurate use.

*Larviciding*

All mosquito larval habitats in all hotspots and evaluation zones will be mapped using handheld GPS systems in January. All habitats found to persist for more than a week within intervention areas will be treated with a larvicide that has been approved by the Pest Control Product Board and by DOMC, *Bacillus thuringiensis var. israelensis* (Bti) and/or *Bacillus sphaericus* (Bs). Larviciding will begin in March 2012 and continue weekly throughout the rainy season (until July 2012).

*Focal screen and treatment (FSAT)*

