## e. Sampling strategy and sample size calculation

The hotspot-targeted intervention will be evaluated inside and outside hotspots of malaria transmission. The latter is the main outcome measure of interest and forms the basis of sample size calculations. All available malaria simulation models indicate that malaria transmission in the area surrounding intervention hotspots would be considerably decreased because malaria transmission is effectively reduced/interrupted in those compounds that seed transmission to a larger geographical area [7-8, 19]. Because there are no published studies on the impact of hotspot targeted interventions, we determined the predicted impact of targeted interventions in our study area by one of the leading individual-based simulation model [19] using human, entomological and parasitological characteristics collected at our sites in Kenya. A previous study on the community benefits of insecticide treated nets in Asembo Bay, western Kenya, indicated that an indirect beneficial effect on malaria transmission may be limited to 500m from the intervention area [20]. We used this finding to define our evaluation zone surrounding the hotspots.

| [figure not shown] |
| --- |

***Figure 3. The predicted impact of untargeted and targeted interventions predicted by an individual-based simulation model.*** *Plotted are smoothed lines, the actual model estimates allow for seasonality.*

We modelled three scenarios in situations with a pre-intervention parasite prevalence in the human population of 5-15%: i) indoor residual spraying (IRS) in an untargeted approach, reaching 20% of the total population (black top line); ii) effective coverage with long lasting insecticide treated nets (LLINs) in an untargeted approach, reaching 80% of the total population (middle dashed grey line); iii) targeted IRS and 95% effective coverage with LLINs in the hotspots (bottom light grey line). The impact of larviciding is currently insufficiently parameterized to be included in the model [19].

We assumed a conservative estimate of the efficacy in detecting hotspots (75%, compared to 93% in Tanzania [[3](#_ENREF_3)]). Our simulations showed that targeted interventions can interrupt transmission completely, both inside and outside hotspots of malaria transmission, reducing overall parasite prevalence from 15% to <0.1%, in a manner that appears sustainable in the following years (see figure 3).

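### The reach of the community effect is measured from the hotspot centre, although hotspots vary in size and the 500 m evaluation zone starts at the hotspot edge

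*Protocol*

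**What the plan says.** Protocol section 10 b (Data analysis) counts the community-wide effect among the key outcomes. It gives the distance analysis this purpose: "To address the question of the distance over which this community-wide effect exists". The method follows: "we will relate parasite prevalence and antibody prevalence to the distance from the centre of the hotspot in intervention and control clusters". The text does not say whether people living inside hotspots enter this analysis, and it does not stratify by hotspot size.

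Elsewhere the protocol measures from the boundary:

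- Section 9 c places the evaluation zone within 500 m of the hotspot's edge, and section 9 e samples the zone on the same basis.
- Section 9 e justifies the 500 m by an earlier bednet study, in which "an indirect beneficial effect on malaria transmission may be limited to 500m from the intervention area".
- Section 9 d (Intervention) directs the package at the hotspots of intervention clusters. Section 12 b says that people living near hotspots get no direct benefit.

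On size and spacing, section 9 c says "Hotspots will be of variable size", sets an upper limit ("Hotspots will be defined as areas that are smaller than 1km^2") and adds "Minimum distance between hotspots will be 1km". No minimum size is given.

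**The concern.** The question is how far an indirect effect reaches beyond treated ground. The natural origin for that is the boundary of the treated area, which is also the origin the protocol uses to lay out its evaluation zone. Distance from the centre equals distance from the boundary plus the hotspot's radius, and the radius differs between clusters.

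Two things follow. First, a given centre distance can lie inside a large hotspot and outside a small one. If hotspot residents are included, the curve in intervention clusters then blends the direct effect with the indirect effect, and in control clusters it blends hotspot with non-hotspot residents, who differ in prevalence by definition. Second, even among outside residents, centre distance is tangled with hotspot size, and the far end of the curve comes only from clusters with large hotspots.

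At stake is the interpretation of the curve as reach, which would inform how wide an area benefits from treating a hotspot.

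**Working it through.** The protocol gives no figure to reproduce here. The check is geometric.

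**Inputs**

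- Upper size limit: 1 km² (section 9 c).
- Lower size limit: not stated, so it is an assumption. The smaller value is one grid cell of 250 × 250 m, or 0.0625 km² (figure 2: "The depicted grid cells are 250x250m"). The larger value is 0.25 km², from the 400 cells in 100 km² of section 9 b (100 / 400 = 0.25).
- Zone width: 500 m from the edge (sections 9 c and 9 e).
- Shape: circles, as an assumption; squares are considered below.

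**Formulas**

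- Radius R = √(A / π).
- A resident at centre distance d is inside the hotspot if d < R, and in the evaluation zone if R ≤ d ≤ R + 500 m.
- Distance from the edge = d − R.

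**Results**

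| Area (km²) | R (m) | Zone, from centre (m) | Resident at 400 m | Resident at 600 m |
| --- | --- | --- | --- | --- |
| 0.0625 | 141 | 141–641 | 259 m outside | 459 m outside |
| 0.125 | 199 | 199–699 | 201 m outside | 401 m outside |
| 0.25 | 282 | 282–782 | 118 m outside | 318 m outside |
| 0.5 | 399 | 399–899 | 1 m outside | 201 m outside |
| 0.75 | 489 | 489–989 | 89 m inside | 111 m outside |
| 0.9375 | 546 | 546–1,046 | 146 m inside | 54 m outside |
| 1.0 (limit) | 564 | 564–1,064 | 164 m inside | 36 m outside |

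1. *Band where inside and outside residents share a centre distance.* It runs from the smallest to the largest radius: 141–564 m with a one-cell minimum, 282–564 m with a 0.25 km² minimum.
2. *Mis-scaling among outside residents only.* The true edge distance at one centre distance can differ by up to 564 − 141 = 423 m, or 564 − 282 = 282 m.
3. *Common stretch of the smallest and largest zones.* This is 564–641 m (77 m wide) or 564–782 m (218 m wide). Beyond 641 m or 782 m, the smallest hotspots contribute nobody.
4. *Square hotspots with evenly spread residents.* At 300–400 m from the centre, the share living inside is 0% for a 250 m side, 6% for a 500 m side and 100% for a 968 m side. Mixing also arises within a single cluster: for the 968 m square, 38% of residents at 500–600 m are inside.
5. *With distance from the edge.* Inside residents lie at or below 0 m and zone residents at 0–500 m in every cluster, whatever the hotspot size. The overlap is zero.

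**Neighbouring hotspots.** Section 9 c does not say between which points the 1 km minimum is measured. If it is edge to edge, two 500 m zones can abut, and the rim of a control zone can lie 1,000 − 500 = 500 m from an intervention hotspot. If it is centre to centre, the gap can be smaller.

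**The case against.** Several objections carry weight.

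- *The protocol keeps the two populations apart.* Objectives, outcomes and sampling all separate hotspots from their surroundings, and a statistical analysis plan could restrict the distance analysis to the evaluation zone. That would remove the mixing of treated and untreated people. The mis-scaling in step 2 would remain, because section 10 b itself fixes the centre as the origin.
- *A one-cell hotspot is unlikely.* Section 9 b surveyed 3,200 compounds in 100 km², or 32 per km², so about 2 per 250 m cell. Section 9 e implies 100 / 35 ≈ 2.9 to 50 / 9 ≈ 5.6 people per compound. Section 9 c estimates the seroconversion rate on subsets of 50 observations. At average density, 50 observations need about 50 / (32 × 5.6) ≈ 0.28 km² to 50 / (32 × 2.86) ≈ 0.55 km². This is indicative only: density varies, and antibody density can stand in for the seroconversion rate. Radii of √(0.28 / π) ≈ 299 m and √(0.55 / π) ≈ 418 m still leave bands of 299–564 m and 418–564 m. The problem shrinks but does not vanish.
- *The edge is not an exact treatment boundary.* Section 9 f lets larviciding extend to habitats on the hotspot fringe. Edge distance is therefore slightly imperfect for that component, but still far closer to distance from treated ground than centre distance.
- *Spacing already limits contamination.* If the 1 km is edge to edge, a control rim 500 m from an intervention hotspot sits at the limit of the spillover that section 9 e assumes. A reader might infer that the analysis counts control residents near an intervention hotspot as the least exposed. The text does not support this as a general statement: it depends on the layout, and the analysis is by arm, so control residents serve as comparators.

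**Conclusion.** The concern holds as a mismatch between the chosen distance and the question. With a smallest hotspot between 0.0625 and 0.25 km² and circular shapes, both assumptions, centre distances from 141 or 282 m up to 564 m can be inside one hotspot and outside another. Among outside residents, distance from treated ground can differ by about 280 to 420 m at the same centre distance. The effect on the estimated reach in prevalence terms cannot be calculated, because the protocol does not give the distribution of hotspot sizes.

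Two stronger readings are tempting and should be resisted. One is that the analysis cannot inform reach at all. At any centre distance the arms are still compared as randomised, so reach is blurred rather than lost. The other is that the trial's main comparison is compromised. The evaluation zone is defined from the edge, so that comparison is untouched, and reach by distance is not among the outcomes listed in section 9 d (Outcomes).

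**What to change.** In section 10 b, replace distance from the hotspot centre with distance from each compound to the boundary of its own hotspot, in both arms, and restrict the analysis to residents outside hotspots. Results inside hotspots are then reported separately, in line with the specific objectives.

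As a sensitivity check for control-zone residents, add distance to the boundary of the nearest intervention hotspot, whichever cluster it belongs to, since hotspots may be only 1 km apart. State whether that 1 km is edge to edge or centre to centre. Note that larviciding may reach the hotspot fringe, so the boundary is approximate for that component.

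The cost is a few lines of wording. Structures were geo-located (section 9 b), coordinates are recorded on the census list and the survey questionnaire (Appendices C and E), and hotspots are referenced to the grid (section 9 c). No new data, sample size or field procedure is involved.

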In the highlands of Western Kenya, malaria transmission is also highly variable despite universal high coverage rates with insecticide treated nets (ITNs) and indoor residual spraying (IRS). In Rachuonyo district, community surveys that were conducted in 2010 indicated parasite prevalences averaging 14.8% but ranging from 0% to 51.5%. School surveys that were conducted in the same year at 46 schools in the district revealed an even more marked variation in children aged 8-14 years where parasite prevalence was on average 25.8% but ranged from 0 to 71.4%. These findings indicate that the current control efforts are insufficient to control or eliminate malaria in parts of the district. One of the reasons that may underlie this apparent failure to interrupt local malaria transmission may be the presence of outdoor biting and resting mosquitoes. Work conducted by the Malaria Transmission Consortium in Rachuonyo has recently indicated that a sizeable proportion of mosquitoes may feed outdoors in the Kenyan highlands [[name] *et al.*, in preparation]. Outdoor biting vectors may remain largely unaffected by control tools that target indoor biting and/or resting mosquitoes like IRS and ITNs. Additional malaria control efforts may therefore be needed in areas where transmission persists: control efforts that reduce malaria transmission regardless of the biting or resting behaviour of the mosquito vector. These targeted interventions are likely to have an impact on malaria transmission in the entire district since small areas with higher malaria transmission intensity form important contributors to overall malaria transmission. Households that are exposed to higher numbers of infected mosquito bites consequently have a higher parasite load in humans. This clustering results in an amplification of malaria transmission: households that are highly exposed to infected mosquitoes also form an important source of malaria infection for uninfected mosquitoes that can spread malaria in the rest of the community [[7-9](#_ENREF_7)]. Hotspots of malaria transmission can thereby increase the efficiency of malaria transmission by a factor 2 to 4 [7-8].

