## b. Study site and population.

Ethnicity in Rachuonyo is predominantly of the Luo ethnic group. Local residents depend upon farming and cattle and goat herding for subsistence. Compounds are distributed broadly across a rolling landscape intersected with small streams and rivers. The main malaria vectors in the area are *Anopheles gambiae*, *An. arabiensis*, and *An. funestus*. Malaria transmission is seasonal, with two seasonal peaks in malaria cases reflecting the bimodal rainfall pattern, with the heaviest rainfall typically occurring between April and June, with a smaller peak between October and November each year. Most malaria is caused by *Plasmodium falciparum*. Community surveys that were conducted in 2010 indicated parasite prevalences averaging 14.8% but ranging from 0% to 51.5%. School surveys that were conducted in the same year at indicated an average parasite prevalence of 25.8% (range 0 to 71.4%).

Detailed cross-sectional surveys have been conducted in an area of 100km^2^ (5x20km) in Rachuonyo district to determine small-scale variations in malaria transmission intensity. (see figure 1). This area was sub-divided into 400 500m^2^ areas referred to as cells.

[figure not shown]

*Figure 1. The Rectangle indicates the area (5*20km) in Rachuonyo district where the activities will take place. Each dot is an individual household. White dots indicate the parasite prevalence in school surveys in the area in the year 2010; colour intensity indicates variation in the altitude. The proposed study area lies at an altitude of 1400-1550 meters.*

All structures in this 5 x 20km area were geo-located by remote sensing and 3,200 compounds were randomly selected for detailed characterization of malaria exposure. After informed consent, household characteristics were recorded for all houses that belonged to the selected compound. Temperatures were taken from each permanent resident of the selected compounds and individuals were asked to provide a single finger-prick blood sample for detection of malaria parasites by PCR [15], malaria-specific antibody responses by ELISA [[12](#_ENREF_12)] and haemoglobin concentration by HemoCue photometer [Angelholm, Sweden]. Febrile individuals were screened in the field using rapid-diagnostic tests [Paracheck, Orchid Biomedical Systems, India] and treated with first line artemisinin-combination therapy.

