Our primary outcome of interest is the impact of hotspot-targeted interventions on parasite prevalence in the area surrounding the hotspot (the evaluation zone). If we evaluate our intervention in 300 randomly selected individuals living outside the hotspot per cluster and assume a conservative estimate of k (0.5 coefficient of variation of true proportions between clusters within each group), we need 8 clusters per arm to detect a reduction from 10% parasite prevalence at baseline to ≤ 5% after the intervention. The actual number of people sampled will depend on the size of the hotspot and surrounding evaluation zone, with a target of sampling 20% of the population in the evaluation zone (≤500m from edge hotspot) or a minimum of 100 and maximum of 500 people. The unit of randomization will be at the compound level therefore 100 people would equate to approximately 35 compounds.

We aim to evaluate the interventions in all age groups above 6 months. If the PCR results of the intensive survey indicates that parasite prevalence is below 10% in certain age groups, these age groups will be considered less suitable for evaluation purposes; they will receive the standard of care provided by the study, including screening and treatment of all febrile cases, but will not be routinely sampled.

To understand possible effect differences between clusters, we also want to determine whether our intervention succeeded in reducing malaria transmission inside hotspots. The estimated parasite prevalence in individuals between 6 months and 20 years of age who are living in hotspots is >20% ([name] *et al.*, unpublished data). With a sample size of 100 individuals per cluster (i.e. per hotspot in 16 clusters), we would be able to detect a reduction to ≤ 5% after the intervention (k=0.5; Z_α/2_=1.96; Z_β_=0.84). Again the actual number sampled will depend on the size of the hotspot, with a target of sampling 20% or a minimum of 50 individuals (approximately 9 compounds).

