During a second visit, one month after initial LLIN distribution the correct usage of LLINs will be evaluated: the correct hanging of LLINs will be confirmed and household members will be asked to explain how they use the net. If needed, instructions about correct use will be repeated and additional nets can be provided if nets are missing or found to be torn. A third visit will occur to re-assess the quality and use of the nets 6 months after the first visit, in conjunction with the second round of IRS. At this point new ownership and quality will be re-assessed and new nets will be distributed as needed. All information on net use and quality will be recorded (appendix D).

*Focal Screening and Treatment (FSAT)*

Screening of a sentinel population within households

The FSAT utilizes individuals aged 6 month to 20 years as a sentinel group to indicate malaria exposure in the household because this age-group experiences the highest parasite burden [23-24]. For this age group all individuals will be tested for parasites using RDTs regardless of presence of symptoms or not. However clinical care will not be restricted to just this age group. All age groups may experience clinical malaria in our setting ([name] *et al.*, in preparation) and therefore those individuals over 20 years who are found to have fever will also be tested by RDT and receive treatment as oart of the FSAT intervention.

The FSAT campaign will take place in intervention hotspots in March 2012; a second round of FSAT is planned to take place in September 2012. Both campaigns will follow identical procedures.

Screening the sentinel group

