   1. YES, WHEN___________
   2. NO
5. Does (NAME) usually stay here?

*L: Bende [NAME] odak ga ka?*

*S: Mtu huyu [NAME] anaishi hapa?*

- 1. YES
  2. NO

1. Did (NAME) sleep here last night?

*L: Bende [NAME] ne onindo ka otieno mokalo?*

*S: [NAME] Amelala hapa jana usiku?*

- 1. YES
  2. NO

1. What is [NAME]'s date of birth?

*L: [NAME] nonyuol e higa ane?*

*S: Tarehe ya [NAME ] ya kuzaliwa?*

YEAR____________

MONTH__________

1. Is (NAME) attending school?

*L: Bende [NAME] dhi ga sikul?*

*S: Je [NAME] anaenda shule?*

- 1. YES
  2. NO

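### The named adjustment variables leave out age, which the protocol ties to parasite burden and records for each participant; adding it is a free safeguard against chance imbalance with 8 clusters per arm

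*Protocol*

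**What the plan says.** Section 10b of the Protocol analyses cluster summaries: "Formal hypothesis testing will be undertaken using stratified unpaired t-tests". On adjustment it says: "Adjustment for covariates will be undertaken replacing the cluster means and proportions with covariate-adjusted residuals from regression analysis of individual-level data". That sentence lists no covariates. A later paragraph of the same section names three: "Additionally, the analysis adjusts for baseline characteristics on malaria infection, haemoglobin concentration and socio-economic status".

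Age appears elsewhere in the Protocol in these roles:

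- **Targeting.** Section 9f (Focal Screening and Treatment) takes people aged 6 months to 20 years as the sentinel group "because this age-group experiences the highest parasite burden".
- **Sampling.** Section 9e allows age groups with PCR prevalence below 10% to be dropped from routine sampling.
- **Serology.** Section 9c fits the seroconversion rate by age and uses age-adjusted antibody densities.
- **Data.** Appendix E, Part III, asks for each person in the house: "What is [NAME]'s date of birth". The census form in Appendix C holds year of birth.

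Section 9g draws participants at random for each survey, with compounds as the sampling step.

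**The concern.** The primary outcome is PCR-confirmed parasitaemia in people of all ages above 6 months. If carriage varies with age, a cluster's prevalence depends partly on the age mix of the compounds drawn. With 8 clusters per arm, chance alone can leave one arm with a younger sample than the other, and the three named variables do not remove that difference.

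Age suits the announced method well. It is an individual-level variable available at each survey, it uses no cluster-level degree of freedom, and treatment cannot affect it. Where each survey has its own random sample, a person seen at follow-up need not have an individual baseline value for infection or haemoglobin, but does have an age.

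What is at stake is a little precision, and credibility if the adjusted result turns on an age difference between arms. Section 9f has clusters allocated in public, so a covariate added only after results are known would be open to question.

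**Working it through.** **1. The plan's own figure, as a baseline.** Section 9e states: "we need 8 clusters per arm to detect a reduction from 10% parasite prevalence at baseline to ≤ 5% after the intervention". Its inputs are 300 people per cluster and k = 0.5. Two-sided 5% and 80% power are given there for the hotspot calculation and are assumed to apply here too. The usual unmatched formula is

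c = 1 + (z_α/2 + z_β)² × [p0(1−p0)/n + p1(1−p1)/n + k²(p0² + p1²)] / (p0−p1)².

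- Within-cluster term: (0.09 + 0.0475)/300 = 0.000458.
- Between-cluster term: 0.25 × (0.01 + 0.0025) = 0.003125.
- c = 1 + 7.849 × 0.003583/0.0025 = 12.25.

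So the 8 per arm is not reproduced. At 8 per arm the noncentrality is 0.05/√(0.003583/8) = 2.36, and power on 14 df is 59.4%. That shortfall belongs to the sample-size section; here 59.4% serves only as the starting value.

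**2. How much noise can age mix cause?** The Protocol gives no prevalence by age in the evaluation zone and no spread of age mix between clusters. Assumed ranges:

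- under-20s make up 50–60% of the sample;
- prevalence ratio, under-20s to older, 1.5 to 3;
- between-cluster SD of the under-20 share, 3 to 10 points. The lower end is sampling alone: √(0.5 × 0.5/300) = 0.029.

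At an overall prevalence of 10% and a 50% share, prevalence in older people is 0.10/(0.5r + 0.5), and in under-20s it is r times that. Cluster SD due to age is the prevalence gap times the SD of the share. The SD of the arm difference is that times √(2/8) = 0.5.

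| Ratio r | Under-20 vs older | Gap | Cluster SD, share SD 3 to 10 points | SD of arm difference |
|---|---|---|---|---|
| 1.5 | 12.0% vs 8.0% | 4.0 points | 0.12–0.40 points | 0.06–0.20 points |
| 2 | 13.3% vs 6.7% | 6.7 points | 0.20–0.67 points | 0.10–0.33 points |
| 3 | 15.0% vs 5.0% | 10.0 points | 0.30–1.00 points | 0.15–0.50 points |

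The planned effect is 5 points.

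**3. Share of the variance.** Control-cluster variance is 0.25 × 0.01 + 0.09/300 = 0.0028. At the top of the ranges age accounts for (0.10 × 0.10)² = 0.0001, or 3.6%. At the bottom (60% share, ratio 1.5) it accounts for about 0.04%.

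**4. Effect on power.** The age part is treated as lying within the k = 0.5 variance and removed in both arms. At the top of the ranges the between-cluster term falls by 0.0001/0.0025 = 4%, and the within-cluster term by 0.25 × 0.10²/0.09 = 2.8%. The variance becomes 0.96 × 0.003125 + 0.972 × 0.000458 = 0.003446, the noncentrality 0.05/√(0.003446/8) = 2.41, and power 61.1%. At the bottom it is 59.5%. The gain is therefore 0.1 to 1.7 points.

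**5. Why it cannot be larger.** Within-cluster sampling is only 0.000458/0.003583 = 12.8% of the variance. Removing all of it would still leave c = 10.8.

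**The case against.** The strongest case against is that a full covariate list commonly sits in a statistical analysis plan, which is not available here. The list in section 10b is not clearly closed either: the sentence on residuals names nothing, the later sentence is worded as an addition, and section 9f says distance to breeding sites has to be allowed for although section 10b does not name it for adjustment. This stands in part. It rules out saying that age is excluded. But the Protocol did choose to name variables, and age is a better-supported candidate on its own evidence.

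It is also fair that no bias is shown. Allocation is random, and chance imbalance is already reflected in confidence intervals built on between-cluster variance. Dropping low-prevalence age groups from sampling would narrow the age mix further. Both points stand.

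A reader might infer more than the document supports in three ways:

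- **Age as the main determinant of carriage.** The Protocol says only that the sentinel ages carry the highest burden. Its Introduction attributes small-area heterogeneity largely to exposure to infected bites.
- **A measured age contrast.** The school figure ("children aged 8-14 years where parasite prevalence was on average 25.8" per cent) and the community average of 14.8% come from different surveys with different sampling frames. Their ratio mixes age with site and sampling, so it is not used above.
- **Elevation as an equal omission.** Elevation is recorded, and in Figure 1 "colour intensity indicates variation in the altitude", but nothing says that it predicts prevalence. The area spans 1400 to 1550 m, only 150 m, and adjustment for baseline infection may already absorb part of any altitude effect. A worthwhile power gain appears only if one assumes a share of between-cluster variance for which the document gives no figure.

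**Conclusion.** The point holds as a modest improvement to a stated method. Section 10b names three adjustment variables and not age, although age is recorded and the Protocol uses it for targeting, sampling and serology. On the assumed ranges, adjustment adds about 0 to 2 points of power to a baseline near 59%, and the chance arm difference it guards against has an SD of about 0.1 to 0.5 points against a planned 5. These sizes rest on assumed age shares, prevalence ratios and between-cluster spread. The case for acting is protection against an unlucky age imbalance and a covariate fixed beforehand; neither invalidity of the unadjusted test nor a material loss of power is shown. Elevation is optional at most.

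**What to change.** In section 10b, add one sentence: age, as bands or a spline, enters the prespecified individual-level regression that produces the covariate-adjusted cluster residuals, for both the evaluation-zone and the hotspot comparisons, with the unadjusted result reported alongside. The same sentence can say whether the list of adjustment variables is closed. If elevation or distance to breeding sites is wanted, decide that now and keep area-level covariates few, given at most 16 clusters. The cost is a line of text; no new data are needed, because date of birth is already on the survey form.
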